### Statistical analysis

The collected data will be coded and stored anonymously in a database created with Excel for Windows software for this purpose. Data will be allocated in tables and graphs for descriptive statistical analysis (mean, standard deviation, absolute and relative frequency distribution). The crossings involving a qualitative variable and a quantitative variable will be performed using parametric and nonparametric comparison tests, according to the distribution of data. The crossings involving two quantitative variables will be performed by calculating correlation coefficients and the crossings between two qualitative variables using association tests. Open questions will be categorized for application of statistical analysis. Continuity and discontinuation rates and their reasons will be evaluated by life table according to Kaplan–Meier. The significance level adopted for the statistical tests will be 5%. For statistical analysis, the Statistical Analysis System (SAS), version 9.4, will be used. All material used for data collection will be stored by the researcher for five years, remaining confidential. The results of the study will be published in an indexed scientific journal. This article has followed the SPIRIT guidelines for its elaboration [16].

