### Follow-up

Participants will be followed on the same service. Between 40 and 60 days postpartum, they should return for postpartum consultation and pelvic ultrasound to assess the IUD and cut the wires (see Table 1). In cases where the woman has an IUD in situ and without visualization of the threads in the cervical canal, the follow-up will be exclusive with pelvic ultrasound. For women who have expelled IUDs or who have IUDs in the cervical canal, a new device of the woman’s preference will be offered. In cases where the woman is not satisfied with IUD, another contraceptive method will be offered and made available.

**Table 1 Tab1:** Procedures and techniques

	Study period					
	Enrollment		Allocation	Post allocation		
	Prenatal consultations	Admission for childbirth	Randomization	Immediately after randomization	In the labor and delivery room following delivery	Postpartum consultations and pelvic ultrasound
**Timepoint**	**T−2**	**T−1**	**T0**	**T1**	**T2**	**T3**

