**Fig. 2 Fig2:**
[figure not shown]
Hand position for IUD protection during insertion

In the puerperal review appointment, carried out between 40 and 60 days by a multidisciplinary team (physician, nurse, and psychologist), a pelvic physical examination will be performed and a questionnaire will be applied to assess, among other questions, the breastfeeding pattern (exclusive, mixed or artificial), bleeding pattern, signs of infection, pelvic pain, return to sexual activity, degree of patient satisfaction with the method, in addition to the desire to continue using the IUD or switch to other methods. When the patient is not sure whether she wants to continue with the IUD or has a transient complaint that can be clinically managed, such as increased bleeding, a new appointment will be scheduled between 30 and 60 days.

Transvaginal ultrasound will be performed at the Hospital’s Diagnostic Imaging Department to assess the proper positioning of the IUD using the Voluson 730 Expert Device, transvaginal, endocavitary probe, transvaginal preset, frequency of 6.5 MHz, mode B, with adjusted focus, gain, and depth. For normal-positioned IUDs and with satisfied patients, the wires will be cut when apparent. For badly positioned IUDs inside the uterine cavity or for those in the endocervical canal, the device will be removed, and a new device will be inserted if the patient desires. In the case of a mispositioned IUD without visible threads, removal will be performed with Hartmann forceps, when possible, or by hysteroscopy. In case of IUD expulsion, the patient will also be offered a new IUD. In the case of uterine perforation, abdominal radiography or a computed tomography scan will be performed to identify the device in the abdominal cavity. The removal will be done by laparoscopy*.* In the case of infection, the patient will be promptly treated with antibiotic therapy and the IUD will be removed if necessary*.* The data referring to the insertions will be analyzed quarterly and presented in the meeting of professors of the obstetrics department of the State University of Campinas to evaluate the feasibility of maintaining the study. In case of the need to modify the protocol of this study after evaluation by obstetrics professors, it will be communicated to the Research Ethics Committee for consideration. Participants will also be communicated at the puerperal review appointment.

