Participants who have complaints related to the intrauterine device and have already attended the postpartum consultation may seek the hospital’s emergency care unit for gynecological evaluation. As many women remain in amenorrhea during lactation, when menstrual cycles return and in case of increased flow or the presence of cramps that bring discomfort, they should also return for a new gynecological evaluation.

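### The planned Kaplan–Meier analysis of continuation and reasons for stopping does not fit a schedule with one assessment for all women and only selective contact afterwards

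*Protocol article*

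**What the plan says.** All quotations are from the protocol article.

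- **Method.** Statistical analysis section: "Continuity and discontinuation rates and their reasons will be evaluated by life table", with Kaplan–Meier named as the method. No time unit, event-dating rule, censoring rule or horizon accompanies this.
- **Contact with all women.** Follow-up section: "Between 40 and 60 days postpartum, they should return for postpartum consultation and pelvic ultrasound to assess the IUD". In Table 1 this visit (T3) is the last column, and expulsion, perforation and positioning are all assessed there.
- **Further appointment for some.** Later in the Follow-up text, after Fig. 2: "When the patient is not sure whether she wants to continue with the IUD or has a transient complaint that can be clinically managed", in which case "a new appointment will be scheduled between 30 and 60 days".
- **Anything later.** The same text leaves further contact to women with device-related complaints, or with heavier flow or cramps once menses return. No later contact is scheduled for a woman who is content with her device.
- **Status of the analysis.** Continuation is not among the listed primary or secondary outcomes. The primary outcome is the expulsion rate. The trial is sized on two proportions, and relations between two qualitative variables are to be examined with association tests.

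**The concern.** Kaplan–Meier needs event times that are known, at least closely, and censoring that is unrelated to the risk of the event. The schedule strains both conditions.

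Up to the visit, displaced devices are mostly found, and malpositioned ones removed, on or after the visit date, and the wish to continue or switch is asked about there. The recorded time then says when the woman came, not when the device failed. If women without an event are censored on their own visit day, those seen at day 40 leave the risk set before those seen at day 60. The few still at risk then carry too much weight.

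After the visit, remaining under observation depends on doubt or dissatisfaction, which are themselves close to the event.

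At stake are the published continuation and discontinuation rates and the split by reason, which would be used in counselling women about this method.

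**Working it through.** The article gives no continuation or discontinuation rate, so there is no stated figure to reproduce. All event rates below are assumptions. From the document come the visit window (day 40–60, which is 21 possible days) and the sample size (93 per arm, 186 in total). Visits are assumed to be spread evenly over the window.

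**1. Daily time, every event dated at the visit, non-events censored at their own visit.** Let p be the true proportion discontinued. When m visit days remain, including the current one, about 1/m of the women still at risk are seen that day and a fraction p of them have the event. The hazard on that day is p/m, so

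1−KM(60) ≈ 1 − ∏ (1 − p/m), m = 1, …, 21.

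| True p | Product formula | Simulation, n = 186 | Ratio to truth (simulation) |
|---|---|---|---|
| 5% | 16.8% | 16.7% | 3.4 |
| 10% | 31.1% | 31.3% | 3.1 |
| 15% | 43.2% | 43.4% | 2.9 |
| 20% | 53.5% | 53.2% | 2.7 |

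Simulation with 93 women gives the same picture (17%, 31%, 43% and 53–54%).

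**2. Some events dated correctly before day 40.** With p = 15%, 1−KM at day 60 is about 32% if half the events carry their true earlier date and about 22% if 80% do. If all do, it is 15%.

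**3. Other rules, same data.** If non-events are censored at a common day 60, 1−KM is 15% for a true 15%, whatever dates the events carry. The same holds for the product-limit estimate with time in whole months, because days 40–60 all fall in the second 30-day month and the visits tie. The curve then adds nothing to the simple proportion.

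**4. Beyond the visit, to day 365.** Three scenarios were assumed: 10%, 15% or 20% stop by the visit, and 5%, 10% or 10% of the rest stop later.

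- True values: 0.10 + 0.90×0.05 = 14.5%; 0.15 + 0.85×0.10 = 23.5%; 0.20 + 0.80×0.10 = 28%.
- Censoring at a common administrative date: correct if every later discontinuation reaches the hospital. If only half do, the expected estimates are 0.10 + 0.0225 = 12.25%, 0.15 + 0.0425 = 19.25% and 0.20 + 0.04 = 24%. The ratios to truth are 0.84, 0.82 and 0.86, an understatement.
- Censoring at last contact: simulated 1−KM is 2.3 to 6.9 times the true value, with 0–30% of continuers returning with complaints and half or all of the later discontinuations seen. Adding the further appointment for 20% of women barely changes this.

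**5. Reasons.** With proportional cause-specific hazards, reason a with cumulative incidence a and all reasons together T, 1−KM for that reason is 1 − (1−T)^(a/T).

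- a = 10%, others 5%: 1 − 0.85^(2/3) = 10.3%
- a = 15%, others 10%: 1 − 0.75^(0.6) = 15.9%
- a = 10%, others 20%: 1 − 0.70^(1/3) = 11.2%

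Treating other reasons as censoring thus inflates the estimate by about 3% to 12% in relative terms.

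**The case against.** The strongest reply is that the article fixes none of the settings that drive the inflation. Time unit, event dating, censoring and horizon are details that an article leaves to the full protocol or the SAP, and under some reasonable choices the bias is nil. That stands. A reader might infer that the planned analysis is bound to overstate discontinuation several-fold. The document does not support this, because steps 3 and 4 show results from an understatement to a large overstatement depending on the rule. Nor is it true that the bias disappears only if every event has its true date: common day-60 censoring or monthly time removes it as well.

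A reader might also infer that the primary comparison is compromised. It is not. Expulsion by insertion method is a comparison of two proportions, for which association tests are planned, and the life table is assigned only to continuation, discontinuation and their reasons. For the same reason the point does not extend to the side-effect outcomes, for which no life table is planned. A distortion between the arms would need visit timing or return behaviour to differ by arm. Both arms share one schedule and nothing in the article suggests such a difference.

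What the reply does not answer is the lack of information after the visit. A SAP can set a censoring rule. It cannot supply follow-up of satisfied women that the schedule does not contain.

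**Conclusion.** The point holds in conditional form. The method named for continuation and its reasons does not match the follow-up described. Up to day 60 it either reduces to the simple proportion or, with daily time and censoring at each woman's own visit, overstates it. The overstatement is about 2.7 to 3.4 times for assumed true rates of 5–20% with all events visit-dated and visits evenly spread, and less if some events have earlier true dates. Beyond the visit, the estimate rests on status that was not observed in the women most likely to be continuing, and its error can go either way. Competing reasons are a minor addition. Because continuation is not a listed outcome and the primary comparison is untouched, this is a cheap improvement and not a threat to the trial's main conclusion.

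**What to change.** Replace the Kaplan–Meier sentence in the Statistical analysis section with the following:

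- By arm, report the proportion continuing and the proportion discontinuing for each reason at the day 40–60 visit, with risk difference and 95% CI. State the number of women whose status is unknown.
- Where true event dates are recorded, and only there, add cumulative incidence by reason up to day 60, with women free of the event censored at a common day 60.
- Report events after the visit descriptively, noting that contact was selective.

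The cost is a short change to the analysis text, with no new data collection. The trial gives up a time-to-event curve that its schedule does not support.

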## Discussion

Insertion of an IUD in the immediate postpartum period has been considered a good option to increase coverage and access to contraception, and its benefit outweighs the inconvenience of a higher expulsion rate. Studies show that it is safe but has higher expulsion rates [17–20].

The vast majority of studies used manual insertion of copper IUDs. Regarding the use of the modified Kelly placental forceps, there are few studies that assess its complications and the comparison between its use and manual insertion [15, 20]. Counseling women is difficult when evidence from randomized controlled trials is limited. The benefit of providing highly effective contraception immediately after delivery may outweigh the disadvantage of the increased risk of expulsion. It is not known whether the use of modified Kelly forceps for immediate postpartum vaginal delivery interferes with expulsion rates compared to manual insertion.

A study comparing both methods of insertion, as well as the degree of discomfort and pain of women undergoing the procedure, is needed. We expect forceps insertion to be a more comfortable alternative for women without labor analgesia, but better placement and a lower expulsion rate are expected with manual insertion by placing the IUD closer to the uterine fundus. Providing access to effective and long-term contraception during hospitalization for childbirth is a fundamental strategy in combating the epidemic of unplanned pregnancy [21].

A high rate of acceptance of the IUD is expected among the women we tend to because at the Women’s Hospital, there is constant training of professionals for insertion of the device, one of the main obstacles mentioned in the literature to the use of the method [22]. There is also a wide dissemination of the benefits of long-term reversible contraceptive methods during prenatal appointments. This is a different scenario from the rest of the country, in which only 2% of women of childbearing age have access to the IUD [7].

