#### Secondary

Infection rate

Perforation rate

Discomfort during insertion

Ultrasound positioning of the IUD

Side effects (increased bleeding and dysmenorrhea)

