### Inclusion and exclusion criteria

The study will include women between 18 and 43 years old, with a single pregnancy, who have vaginal birth, who wish to use the IUD as a contraceptive method, and who do not have contraindications, namely, uterine malformation; uterine fibroids that deform the cavity; diagnosis or suspicion of ovular infection; diagnosis or suspicion of infection elsewhere; active sexually transmitted infection; and severe anemia (hemoglobin less than 8.0 mg/dl during antenatal care). Women who, after signing the consent form and randomization, wish to withdraw from the study for any reason, present with fever during labor or delivery, rupture of amniotic membranes for more than 24 h, manual extraction of the placenta, postpartum hemorrhage or uterine atony will be withdrawn from the study.

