### Intervention

The possibilities of postpartum contraception and the benefits of starting a method before hospital discharge will be discussed during antenatal consultations or on admission for childbirth for women with external antenatal care. Women who want the copper IUD as a contraceptive method will be informed about its durability, side effects, advantages, and disadvantages of its insertion after placental delivery. Women who wish to participate in the study will be randomly assigned to one of the groups (forceps or manual insertion), through a computer-generated numerical allocation list. Randomization will be kept confidential in a sealed envelope until the time of insertion. In the immediate postpartum period, the copper IUD will be inserted according to the result of the randomization. Only members of the research group, with specific training, will be able to insert the IUD after signing the consent form by the patient. Study participants will remain unsure to which group they were allocated.

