**Assessments:**						
**Pain or discomfort during insertion**					x	
**Expulsion**						x
**Uterine perforation**						x
**Proper positioning**						x

Orientation, insertion, and removal of misplaced IUDs will be performed by a group of trained resident physicians and supervised by an experienced chief. To guarantee the standardization and constant review of the technique, periodic training offered by the researchers is planned. After insertion, the professional responsible for the procedure is recorded so that we can later correlate whether the expulsion and/or mispositioning was influenced by the experience of the professional who performed the procedure.

The insertion technique will be briefly described below. For insertion with the forceps, the patient must be in a lithotomy position with the feet or knees supported. Asepsis of the vulva, vagina, and cervix will be performed with aqueous chlorhexidine solution. The uterus will be palpated to assess the fundus and tone. The evaluator must wear sterile gloves and must gently insert the vaginal speculum. The anterior labrum of the cervix should be clamped with a Collin clamp. The physician’s nondominant hand rested on the uterine fundus. The IUD should be secured using modified Kelly forceps (see Fig. 1). The physician's nondominant hand rested on the uterine fundus, and the IUD was gently placed through the cervix using forceps. The forceps must then be opened and withdrawn completely from the side. The clamp from the labrum of the cervix and the vaginal speculum should both then be removed.

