### Sample size

To calculate the sample size, the proportion between 2 groups method for comparison was used, setting the level of significance alpha or type I error at 5% (alpha=0.05) (or 95% confidence interval) and the power of the sample at 80% (or 20% type II error (beta=0.20)), according to Hulley et al. (2007) [14], and using the expulsion ratio values after IUD insertion in vaginal delivery in each group, obtained from a literature article [15]. Based on the results, it was estimated that a sample of *n*=186 women (*n*=93 with manual insertion and *n*=93 with forceps) would be representative for comparison of expulsion between the 2 groups.

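### The comfort expectation is confined to women without labor analgesia, but the discomfort outcome and its analysis, as worded, make no use of analgesia, so an expected effect could be diluted

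*Protocol article*

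**What the plan says.** The Discussion of the protocol article states the comfort expectation conditionally: "We expect forceps insertion to be a more comfortable alternative for women without labor analgesia". This is the article's only mention of labor analgesia. The sentence before it is broader. It says that a study comparing the two methods, "as well as the degree of discomfort and pain of women undergoing the procedure, is needed", without singling out any group.

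The rest of the article is equally general:

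- **Eligibility** (Inclusion and exclusion criteria): "The study will include women between 18 and 43 years old, with a single pregnancy, who have vaginal birth". No criterion concerns analgesia.
- **Outcome** (Secondary): "Discomfort during insertion", with no condition attached.
- **Schedule** (Table 1, Assessments): "Pain or discomfort during insertion" is marked once, in the delivery room. Analgesia is not an item.
- **Allocation** (Intervention): "through a computer-generated numerical allocation list". No stratification is stated, and the result stays in a sealed envelope until insertion.
- **Analysis** (Statistical analysis): "The crossings involving a qualitative variable and a quantitative variable will be performed using parametric and nonparametric comparison tests". This is a rule by type of variable. It names no outcome, covariate or subgroup.

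**The concern.** The authors name analgesia as the condition under which they expect a difference in comfort, and the described analysis then does not use it. Women with effective analgesia at insertion may feel little with either technique. Mixing them in would have two effects. It shrinks the arm difference in proportion to their share. It also adds the large pain gap between women with and without analgesia to the variance.

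Discomfort is one of the four outcomes in the stated aim. The Discussion expects manual insertion to do better on placement and expulsion, so comfort is the only advantage it expects of forceps. If that difference exists and is missed, one side of the trade-off behind the choice of technique is lost.

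**Working it through.** **The plan's own figure.** The only calculated figure is 93 women per arm, for expulsion, with "setting the level of significance alpha or type I error at 5% (alpha=0.05" and 80% power. The expulsion rates behind it are not printed, so it can be neither reproduced nor refuted (17% versus 35%, for example, returns 93 per arm without continuity correction). It serves here only as the number of women available. There is no planning figure for discomfort.

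**Inputs from the document.** 93 per arm; alpha 0.05, taken as two-sided because the side is not stated.

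**Assumed inputs (the document gives none).** A 0-10 scale. Without analgesia: means 5.75 (manual) and 4.25 (forceps), SD 2.5. With analgesia: mean 1, SD 1 in both arms. Share with analgesia *a* from 10% to 70%; *q* = 1 − *a*.

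**Formulas.** Power = Φ(D/SE − 1.96) throughout.

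1. Unadjusted, all women: D = 1.5*q*. The variance in an arm whose no-analgesia mean is *m* is 6.25*q* + *a* + *qa*(*m* − 1)². SE = √[(sum of the two arm variances)/93].
2. Adjusted for analgesia (strata weighted by size), all women: D = 1.5*q*, SE = √[2(6.25*q* + *a*)/93].
3. Women without analgesia only: D = 1.5, SE = √[2 × 6.25/(93*q*)].

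**Worked at *a* = 50%.**

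1. The arm variances are 3.625 + 0.25 × 4.75² = 9.27 and 3.625 + 0.25 × 3.25² = 6.27. SE = √(15.53/93) = 0.409; 0.75/0.409 = 1.84; power 45%.
2. SE = √(2 × 3.625/93) = 0.279; 0.75/0.279 = 2.69; power 77%.
3. SE = √(12.5/46.5) = 0.518; 1.5/0.518 = 2.89; power 82%.

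| Share with analgesia | Difference in all women | Power, unadjusted | Power, adjusted | Without analgesia, per arm | Power, that group only |
|---|---|---|---|---|---|
| 10% | 1.35 | 93% | 97% | 84 | 97% |
| 20% | 1.20 | 83% | 95% | 74 | 96% |
| 30% | 1.05 | 71% | 91% | 65 | 93% |
| 50% | 0.75 | 45% | 77% | 46 | 82% |
| 70% | 0.45 | 24% | 48% | 28 | 61% |

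**A second set of assumptions.** Take an effect of 0.5 SD without analgesia, none with it, and equal pain levels otherwise. Unadjusted power is then Φ(0.5*q*√(93/2) − 1.96), against Φ(0.5√(93*q*/2) − 1.96) in women without analgesia. At 20%, 30%, 50% and 70% analgesia this gives 78% versus 86%, 67% versus 81%, 40% versus 67%, and 17% versus 46%. The ordering is the same. If pain also differs by 1 SD between women with and without analgesia, unadjusted power falls to 72%, 58%, 33% and 15%.

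**Chance imbalance.** At 50% analgesia the 95% range for the difference between arms in analgesia share is ±1.96√(2 × 0.5 × 0.5/93), about 14 percentage points. With an average pain gap of 4 points, that could shift a single trial's estimate by about 0.14 × 4 ≈ 0.6 point. This is already counted in the unadjusted SE: the squared SEs in steps 1 and 2 differ by 0.25 × (4.75² + 3.25²)/93 = 0.089, and 1.96√0.089 ≈ 0.6.

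**Weights matter in a stratified analysis.** Inverse-variance weights would favour the less variable analgesia stratum, where no difference is assumed. At 50% the weights are 46.5/12.5 = 3.72 and 46.5/2 = 23.25. The estimate falls to 1.5 × 3.72/26.97 = 0.21 with SE 1/√26.97 = 0.193, and power to about 19%.

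**The case against.** The strongest reply is that only a condensed article is available. Recorded covariates, adjustment and subgroups are commonly left to the full protocol or analysis plan, so their absence here proves nothing. Table 1 is visibly incomplete: it omits infection and side effects, which are named secondary outcomes. The analysis text is generic and does not rule out a comparison by analgesia. This stands. A reader might infer that the article commits to an unadjusted comparison in all women, or that analgesia goes unrecorded. It says neither. What remains is that a specific expectation and a general outcome and analysis, both printed, do not meet.

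Second, the aim and the sentence before the expectation concern women in general. A reader might infer that the trial's real question is confined to women without analgesia, so that they should form the main comparison. The document does not support that: the restriction appears in one Discussion sentence, and putting a subgroup ahead of all randomized women is a debatable choice of estimand. Under the assumptions above, adjustment recovers most of the loss at analgesia shares up to 50% while keeping every woman.

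Third, the size rests on assumed figures, and with little analgesia the loss is small (93% against 97% at 10%). This also stands.

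**Conclusion.** The point holds as a mismatch. The expectation is conditional on analgesia, and the outcome and analysis as worded do not use it. If the benefit is confined to women without analgesia, a simple comparison in all women is diluted and noisier. Under the main assumptions its power is 93%, 71%, 45% and 24% at 10%, 30%, 50% and 70% analgesia, against 97%, 91%, 77% and 48% with adjustment. The direction follows from the arithmetic; the size depends on the analgesia share and the effect in each group, neither of which is given.

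Two stronger readings are not supported:

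- A reader might infer that chance imbalance in analgesia biases the comparison. Under randomization it is random error, already contained in the unadjusted variance, and adjustment reduces it.
- A reader might infer that a missed comfort difference would leave the choice resting on expulsion alone. Perforation, infection, ultrasound positioning and side effects are also outcomes.

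Discomfort is secondary and the trial was sized for expulsion, so the primary conclusion is unaffected. This is an improvement worth making, not a flaw that threatens the trial.

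**What to change.** 1. Record labor analgesia (yes/no and type, from the delivery record) as it stood before the allocation envelope is opened. The envelope stays sealed until insertion, so this is a valid baseline variable. For the 30 women already included it could be taken from the same record, assuming the record holds it.
2. In Statistical analysis, prespecify the discomfort comparison in all women, adjusted for or stratified by labor analgesia. If stratified, weight the strata by size, not by inverse variance.
3. Prespecify and report the estimate in women without labor analgesia, with the technique-by-analgesia interaction, as the test of the expectation in the Discussion.

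If a fuller document already does this, one aligning sentence in the article is enough. If the authors mean the expectation to cover all women, they can reword that sentence instead.

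The cost is one data field and a changed analysis sentence, with no added visit or procedure. The downside is that the estimate in women without analgesia is less precise, since it rests on fewer women: 46 per arm at 50% analgesia, 28 at 70%.
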